## Abstract

**Background:**

Depression is a common mental health issue that can be effectively managed in primary and community health care settings. However, there is a significant gap between the number of individuals in need of care and those who actually receive treatment, with the greatest gap in low- and middle-income countries (LMICs). Although efforts have been made in LMICs to improve access to mental health services by addressing supply-side barriers, there has been less attention to demand-side obstacles. On the demand side, factors such as stigma, negative attitudes, and limited awareness of available services lead to underutilization of mental health services. This protocol describes a study of active ingredients of a community-based intervention aimed at enhancing help-seeking for depression care in Nepal, a LMIC with low rates of mental health treatment seeking.

**Methods:**

The study will take place in two municipalities in eastern Nepal, utilizing the Multiphase Optimization Strategy (MOST) with a 2 × 3 factorial randomized controlled trial design. Female Community Health Volunteers will be trained to identify individuals with depression using the Community Informant Detection Tool, a proven community-based strategy for proactive case detection, and subsequently implement the Gain Life intervention, which aims to promote help-seeking for depression care. The Gain Life intervention comprises four components: (i) information about depression, (ii) awareness of available services, (iii) stigma reduction by dispelling myths and facts about depression, and (iv) a life transformation story. The study will target the adult population, with eligibility criteria including being 18 years or older, residing in specific municipalities, meeting the CIDT threshold for depression, providing consent, and having proficiency in Nepali. The sample size will be 288, with the primary outcome being help-seeking behaviour.

**Discussion:**

In this protocol paper, we outline how the MOST framework can optimize a community-based intervention aimed at improving help-seeking for depression care. The findings from this study will guide decisions on whether to proceed with a fully randomized controlled trial or conduct an additional optimization study to finalize the intervention components.

**Trial registration:**

ClinicalTrials.gov NCT06574074. Registered on 27 August 2024.

## Introduction

Depression is a prevalent mental health condition that imposes significant emotional and financial burden on individuals, families, and communities [22, 25, 35, 56]. It is estimated that over 322 million people globally are affected by depression [76], accounting for 40.5% of disability-adjusted life years (DALYs) caused by mental illness [74]. It is associated with increased risk of suicide, type-2 diabetes, and heart disease [4, 38, 64] with over 50% of suicide victims having depression [64]. Women are reported to be 2 to 3 times more likely to experience depression than men [51, 73], with a higher risk during the perinatal period, from pregnancy to one year post-delivery [2, 23, 58, 73].

Depression is a treatable and potentially preventable condition [3]. Timely and appropriate help-seeking is crucial for early detection, treatment, and recovery [16]. Research has shown that depression and other mental health conditions can be effectively treated in primary and community health care systems through a task-sharing approach [7, 34, 37]. Despite the availability of evidence-based cost-effective interventions for depression, there is a significant gap between the number of individuals in need of care and those who receive treatment [8, 9, 28, 34, 63, 70, 75]. Studies have reported that 86.3% of people with anxiety, mood, or substance disorders in lower-middle-income countries received no treatment [20]. Additionally, individuals with depression often prefer seeking help from informal sources such as traditional healers, friends, or family members rather than professionals like doctors, psychiatrists, or psychologists [65, 66].

Nepal has made significant strides in improving access to mental health care. Initiatives include translating and adapting the WHO mental health gap action programme intervention guide (mhGAP-IG) for use in Nepal [46], developing a national mental health strategy and action plan [57], creating mental health training manuals for health care providers [41, 44], providing free psychotropic medicines at the lowest level of health care facilities [71], and establishing a standard treatment protocol [43]. The World Health Organization (WHO) has been supporting the government in implementing and scaling up mental health services throughout the country through its special initiatives [55]. Despite these efforts, a large proportion of people (77%) with mental health conditions in Nepal do not receive any treatment [62]. The main reasons for not seeking mental health services are related to individuals’ attitudes and intentions towards mental health problems. For example, the national mental health survey revealed that approximately half of the participants who did not seek care believed that the problem would resolve on its own (48%), followed by a willingness to solve the problem independently (47%), and the perception that they did not have mental health issues (46%) [62].

The underutilization of mental health services in many low- and middle-income countries (LMICs) can be influenced by various factors, including structural and attitudinal barriers. Efforts have been made to improve the availability of mental health services by addressing supply-side barriers through a task-sharing approach and reducing structural barriers. However, demand-side barriers, such as low perceived needs, stigma, and negative attitudes towards mental health treatment, are often overlooked [1]. Stigma and negative attitudes towards mental health care significantly contribute to the underutilization of services and are crucial barriers to seeking help [12, 30, 59, 68]. Internalized stigma is linked to reduced help-seeking behaviour or negatively affects help-seeking [10, 11]. Poor mental health literacy, lack of knowledge about available services, lack of trust in services, cultural practices and beliefs, and low detection within the family are other significant barriers to accessing mental health services [1, 5, 18, 26, 30, 45, 47, 67].

Research has shown a positive relationship between mental health literacy and help-seeking behaviour, indicating that improved mental health literacy can increase the likelihood of seeking help [29, 72]. Similarly, individuals’ attitudes and intentions toward seeking help can predict future behaviour [69], emphasing the importance of interventions that promote positive attitudes toward mental health care to encourage actual help-seeking behaviour [27]. Social-contact-based interventions involving education and personal recovery stories have been used to reduce mental health stigma [50] including in Nepal [40], but they often yield only short-term results [54]. These findings suggest a need for evidence-based interventions to improve help-seeking behaviour for mental health care.

This study aims to develop a community-based intervention to address barriers to seeking help for depression by focusing on improving mental health literacy, increasing awareness of available mental health services, dispelling myths and misconceptions about depression, and changing negative attitudes towards depression care through a recovery story from someone who has experienced depression. The intervention was developed through a systematic review, qualitative study, and input from various stakeholders, including individuals with lived experience and mental health experts. This paper outlines the intervention, the evaluation methods used to assess its delivery strategies, and the testing of its feasibility, acceptability, and appropriateness.

## Methods

### Objective

The aim of this study is to analyze the active components of Gain-Life (Give informAtIoN to transform Life), a community-based intervention designed to promote help-seeking for depression care. The study will examine the effects of intervention components including information on depression, awareness of treatment options, stigma reduction, dispelling myths about depression, and sharing personal transformation experiences, on help-seeking behaviour as the primary outcome and treatment adherence as secondary outcomes. Furthermore, the study will evaluate the delivery methods and assess the feasibility, acceptability, and appropriateness of Gain-Life intervention in encouraging help-seeking for depression care.

The primary research question of this study is to determine which component of the Gain-Life intervention has a positive impact on the primary outcome of help-seeking behaviour among individuals with depression. This outcome is measured as the percentage of people seeking care from a health care provider within one month of receiving the intervention.The secondary research question aims to evaluate the intervention’s effects on different outcomes, such as treatment adherence, reduction in depression symptom severity, and the feasibility, acceptability, and appropriateness of Gain-Life in promoting help-seeking for depression treatment.

### Setting

The study will be conducted in two municipalities in the Morang district of eastern Nepal. Morang is one of the most populous districts in the country and also diverse in caste/ethnicity, language, and geography. The total population of Morang district is 1,148,156 according to the 2021 census [61]. The selection of Patharisanischare municipality and Kanepokhari rural municipality for this study was purposeful taking into account factors such as diversity in caste/ethnicity and language, absence of mental health services, lack of FCHVs trained in the community informant detection strategy, and the willingness of local government to provide support. The combined population of Kanepokhari (43,193) and Patharisanischare (72,451) is 115,544 with 54,389 males and 61,255 females [61]. There are 28,643 households, with 10,663 in Kanepokhari and 17,980 in Patharisanischare. The literacy rates in Patharisanischare (81.5%) and Kanepokhari (77.8%) are slightly higher than the national average of 76.2%. Patharisanischare has 10 health facilities (1 municipal level hospital, 2 health posts, and 7 rural health centers), while Kanepokhari has 7 health facilities (1 municipal level hospitals, 2 health posts, and 4 rural health centers). The number of FCHVs in Kanepokhari (*n* = 24) is slightly lower than in Patharisanischare (*n* = 30).

### Study design

This is a single-blinded, individually randomized factorial trial. Behaviour change interventions are complex due to the many interacting components involved [15]. While traditional randomized controlled trial (RCT) designs are considered the gold standard for evaluating the impact of an intervention, they typically do not identify which specific components contribute to desired outcomes [13]. In contrast, factorial design enables the assessment of individual intervention components and their interactions [36]. This approach is appropriate for enhancing the effectiveness, efficiency, and cost-effectiveness of an intervention, ultimately facilitating its scalability to benefit a large population [14].

In this study, we will utilize a Multiphase Optimization Strategy (MOST), an engineering-based approach aimed at effectively optimizing behavioural interventions [13]. MOST comprises three key phases: preparation, optimization, and evaluation. The preparation phase involves developing a conceptual model for the intervention and piloting it to identify “core components” and determine the optimization criteria (e.g. effectiveness, efficiency, cost). The optimization phase utilizes a multifactorial design to conduct a randomized factorial experiment trial using the specific components identified during the preparation phase. Finally, the evaluation phase involves reviewing the trial results and reaching a consensus on the way forward. We will conduct a 2 × 3 factorial individually randomized, single-blinded controlled trial design. Participants detected by Female Community Health Volunteers using the CIDT, will be randomized into one of eight possible combinations of three candidate intervention components ranging from none to all three components (*n* = 36 in each condition). All participants will receive component one, i.e. information about depression. However, the three candidate intervention components, each with two options, include the following: (a) information about available services (on/off), (b) addressing stigma and discrimination (on/off), and (c) life transformation recovery stories (on/off). All four intervention components will be delivered in person on a one-to-one basis.

### Participants and eligibility criteria

The study will be conducted with an adult population. The eligibility criteria for participation in this study include being an adult aged 18 or older residing in Kanepokhari Rural Municipality or Patharisanischare Municipality, those detected through CIDT for depression, providing written consent for participation, and being proficient in speaking and understanding Nepali. Participants receiving mental health services will be excluded from the study. In Nepal, FCHVs, the lowest level of health workers, will receive training to incorporate CIDT into their regular responsibilities. When FCHVs encounter someone in the community matching the narrative, they ask two additional questions about the impact of the condition on daily activities and the individual’s willingness to seek help [31]. If the person meets the criteria and responds positively to at least one of the two questions, FCHVs will schedule the Gain Life intervention.

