### Recruitment

Participants will be purposefully recruited through a systematic process. Trained FCHVs will identify potential participants who meet the CIDT criteria, such as individuals whose personal experiences align significantly with the CIDT story, exhibit impaired daily functioning, and express a need for support. Once identified, FCHVs will provide the details (age, gender, location) of individuals who meet CIDT criteria to their supervisor via a phone call. The supervisors will assess the eligibility criteria (i.e. 18 years or older, ability to speak, and CIDT threshold) and send the case details to the first author ([name]) for randomization.

Bi-monthly group meetings will be held for FCHVs to share their progress, discuss challenges encountered during the implementation of the CIDT, and provide motivation. Supervisors will also conduct field visits to offer immediate feedback and enhance FCHVs’ skills in utilizing the CIDT to ensure an effective recruitment strategy.

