### Implementation process of Gain Life intervention

FCHVs will utilize the CIDT in their daily tasks to identify individuals experiencing depression. They will initially consider individuals whose experiences resonate with the CIDT vignette. Upon identifying a potential candidate, FCHVs will engage in a consultation to evaluate the impact of the issue on the individual’s daily life and their readiness to seek assistance. If the individual agrees to participate in the Gain Life intervention, FCHVs will arrange a suitable date and time for its implementation.

As per the study protocol, participants may receive all four components of the Gain Life intervention or a combination of three, two, or one component. FCHVs will coordinate the intervention implementation accordingly, with a maximum of two components being delivered simultaneously. In cases where three components are required, they will be administered on separate days. The intervention sessions will take place in confidential settings, such as the participant’s or FCHV’s residence, to ensure privacy. While family members are encouraged to join, participants who prefer not to involve them can opt for individual sessions.

Participants may choose not to receive all allocated components of the intervention for reasons such as feeling that they do not need the additional components, starting treatment after receiving initial components, or other contextual factors. These participants will still be included in the analysis using an intention-to-treat approach. Additionally, there will be no restrictions on participants receiving other interventions, support, or attending awareness programmes. These aspects will be explored in the qualitative component of the intervention.

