### Moderators

We will assess how socio-demographic factors such as caste/ethnicity, age, gender, education level, occupation, and religion moderate the intervention’s impact through general linear regression models and interaction variables. Previous studies in Nepal have shown that gender, caste/ethnicity, and occupation can affect rates of depression and anxiety [39, 48]. These analyses are crucial for promoting equitable access to mental health care in Nepal.

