## Discussion

In this study, we utilized the MOST framework to optimize a community-based intervention aimed at increasing help-seeking for depression care. Through a factorial design, our goal is to develop an effective intervention that raises awareness about depression, available services, and reduces stigma. The study will examine the impact and interaction of intervention components such as depression information, treatment awareness, dispelling myths, and life transformation experiences. The primary outcome will be changes in help-seeking behaviour, with treatment adherence as a secondary outcome.

The strengths of our study include the following: (i) the use of multiple methods and stakeholders in the development of the intervention, such as a systematic review, formative study, consultative workshops with various stakeholders, and pilot testing with a group of 10 FCHVs in another district; (ii) while most global mental health research focuses on developing and evaluating interventions to address supply-side barriers, this study targets demand-side barriers by using the innovative study design MOST, enabling us to evaluate the effectiveness of intervention components through an iterative optimization process; and (iii) the implementation of the intervention and study in multicultural, multilingual, and multi-ethnic communities in eastern Nepal, allowing for generalization of results throughout Nepal.

We anticipate challenges in maintaining intervention fidelity, as participants may seek additional information from FCHVs beyond what is included in the intervention packages or in a particular component. Additionally, ensuring fidelity in delivering the core components and the combination of intervention packages by the same FCHVs may be challenging. To address this, fidelity checklists will be used to guide delivery, and regular supervision sessions will be conducted to support FCHVs in maintaining fidelity.

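### The nationwide generalisation claim goes beyond the design, the pre-randomisation willingness answer has no stated role in the analysis, and two sections give different entry rules.

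*Protocol article*

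**What the plan says.** **Entry.** Under Participants and eligibility criteria, volunteers who meet someone matching the CIDT narrative "ask two additional questions about the impact of the condition on daily activities and the individual’s willingness to seek help". A person qualifies who "responds positively to at least one of the two questions". Proficiency in Nepali is also required. Recruitment describes people meeting the CIDT criteria as those who match the story, "exhibit impaired daily functioning, and express a need for support". The Implementation process section adds that volunteers "evaluate the impact of the issue on the individual’s daily life and their readiness to seek assistance" before the person agrees to take part.

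**Role of willingness.** The Introduction says that "attitudes and intentions toward seeking help can predict future behaviour". The primary outcome is help-seeking within one month. The planned moderators are "socio-demographic factors such as caste/ethnicity, age, gender, education level, occupation, and religion moderate the intervention". The baseline examples under Quantitative data analysis are age, sex, caste/ethnicity and education. The knowledge, stigma and service-awareness scales are taken at three months and expressly not at baseline.

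**Reach.** Two municipalities of Morang district were chosen purposefully. The criteria were diversity in caste/ethnicity and language, then "absence of mental health services, lack of FCHVs trained in the community informant detection strategy, and the willingness of local government to provide support". Local primary care workers had no mental health training and receive it as part of the study. The Discussion lists as a strength the "multicultural, multilingual, and multi-ethnic communities in eastern Nepal, allowing for generalization of results throughout Nepal". The limitations paragraph mentions neither the choice of sites nor the language rule.

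**The concern.** There are three linked issues.

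1. The nationwide claim is an affirmative statement in the protocol, not a detail left to another document. It rests on linguistic diversity, yet entry is limited to people proficient in Nepali. It also rests on two sites picked partly for local government support and for a lack of services that the study then supplies. A reader deciding which components to carry forward could take the result further than it goes.

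2. By the protocol's own account, willingness to seek help should predict the primary outcome, and it is asked about before randomisation. It is the only measure of attitude or intention from before randomisation that the document names. Giving it no analytic role forgoes some precision. It also leaves unclear how the components perform in reluctant people, although the Introduction presents low perceived need and negative attitudes as the barriers to be addressed.

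3. The two accounts of entry describe different samples. Under one, impaired people who are unwilling can enter. Under the other, if need for support means willingness, they cannot.

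**Working it through.** **Sample size, to see whether anything here disturbs it.** Inputs from Sample sizes and sampling process: 40% vs 60%, 90% power, alpha 0.05 (two-sided assumed), 8 conditions of 36. Each main effect therefore compares 144 with 144.

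Uncorrected n per level = [1.96·√(2·0.5·0.5) + 1.2816·√(0.24 + 0.24)]² / 0.20² = 2.274² / 0.04 ≈ 129.3, rounded up to 130 (260 in total). With continuity correction it is 140 per level, 280 in total, which is close to the stated 288. Power at 144 vs 144 is 92.8%. Nothing below alters this, because entry precedes randomisation.

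**How far entry favours willing people.** Let w be the willing share and i the impaired share among CIDT matches. The document gives neither, so both are assumed, and independence is assumed too. Under the either-question rule:

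P(willing | entered) = w / [1 − (1 − w)(1 − i)]

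| w before | i | willing share after entry |
|---|---|---|
| 0.5 | 0.3 | 0.5/0.65 = 0.77 |
| 0.5 | 0.5 | 0.5/0.75 = 0.67 |
| 0.5 | 0.7 | 0.5/0.85 = 0.59 |
| 0.5 | 0.9 | 0.5/0.95 = 0.53 |
| 0.2 | 0.9 | 0.2/0.92 = 0.22 |

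The share rises in every row, but possibly by very little. Under the Recruitment wording, reading need for support as willingness, it would be 100%.

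**Precision from adjusting for willingness.** Let a and b be the help-seeking rates in willing and unwilling entrants, w now the willing share among entrants, and P = wa + (1 − w)b. All are assumed. The plan fits general linear models, so on the risk-difference scale:

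R² = w(1 − w)(a − b)² / [P(1 − P)]; standard-error ratio = √(1 − R²)

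Worked example for a = 0.60, b = 0.25, w = 0.5: P = 0.425, R² = 0.25·0.1225/0.2444 = 0.125, ratio 0.935.

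| a vs b | w = 0.5 | w = 0.85 | cut in SE |
|---|---|---|---|
| 0.55 vs 0.35 | 0.980 | 0.990 | 1% to 2% |
| 0.60 vs 0.25 | 0.935 | 0.968 | 3% to 6% |
| 0.60 vs 0.15 | 0.885 | 0.947 | 5% to 12% |

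**Power of a willingness-by-component test.** Assume a 20-point effect in willing entrants and none in unwilling entrants, with a 40% control rate in both. Taking the variance as 0.24 in every group:

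v = 0.48/(144w) + 0.48/[144(1 − w)]; power = Φ(0.20/√v − 1.96)

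- w = 0.5: v = 0.0133, power 41%
- w = 0.7: v = 0.0159, power 36% (35.5%)
- w = 0.9: v = 0.0370, power 18%

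**Claim against design.** No calculation applies. The Discussion's inference is to the whole country. Setting and the eligibility section define two non-randomly chosen municipalities of one district and a language restriction. The limitations paragraph does not connect the two.

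**The case against.** The strongest reply is that covariates and subgroups belong in a statistical analysis plan, that the baseline examples are introduced as examples, and that omitting a prognostic covariate is not an error. That stands: adding willingness improves the plan and does not repair a mistake. It does not fully dispose of the point, because the moderators are described as socio-demographic, a class that does not contain willingness, and a later plan cannot use an answer that was not kept.

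Several stronger readings are tempting, but the documents do not support them:

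- A reader might infer that the sample consists of people already willing to seek help. Under the eligibility section impairment alone suffices, and the shift may be as small as 0.50 to 0.53.
- A reader might infer that the answer is unused or discarded. It serves as an entry criterion, and supervisors check the CIDT threshold, so more than age, gender and location may reach them. The full content of the baseline interview is not shown.
- A reader might infer that the literacy content could be wrongly judged inactive. Everyone receives information about depression, so it is not a tested factor. The services component addresses not knowing where to go, which can hold back willing people too.
- A reader might infer that the component comparisons are biased. They are not, since randomisation follows entry.
- On sites, diversity is the first-listed selection criterion and does support some breadth. Proficiency in Nepali does not exclude multilingual people, and no exclusion rate is given. Neither fact carries the result from two chosen municipalities to the whole country.

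**Conclusion.** The point holds in three limited parts.

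1. The nationwide statement claims a property that the design lacks and should be restricted. This needs no assumption.

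2. The willingness answer is obtained before randomisation, and the protocol itself treats intentions as predictive, but it has no stated role in the analysis. Using it would reduce main-effect standard errors by about 1% to 12%, with 3% to 6% in the middle scenario. Those figures depend wholly on assumed willing shares (50% to 85%) and assumed help-seeking rates. A willing-versus-unwilling comparison of component effects would have about 18% to 41% power even if the whole effect were confined to willing entrants, so it can only be exploratory.

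3. The eligibility and Recruitment sections give different entry rules. The documents do not show which was applied, and the difference determines how far the sample is limited to willing people.

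All three concern interpretation and efficiency. The randomised comparisons and N = 288 are unaffected.

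**What to change.** - **Discussion:** replace the nationwide statement with one limited to CIDT-positive, Nepali-proficient adults in similar municipalities with newly introduced services. Add the purposeful choice of sites and the language rule to the limitations. Cost: a few sentences.
- **Entry rule:** reconcile the eligibility section with Recruitment, and state which rule was actually applied. Cost: a clarification.
- **Data:** record both CIDT answers (impact and willingness) for every participant and report their distribution. For those already enrolled, recover them from CIDT forms completed at detection. Asking again after the intervention would not give a pre-randomisation value. Cost: two fields. Delivery began in June and baseline collection in July 2024, so some early entrants may lack the value; if it cannot be recovered, say so as a limitation.
- **Analysis:** before unblinding, pre-specify willingness as a covariate in the primary model and state how missing values will be handled. Add willingness by component to the moderator analyses, labelled exploratory and reported with confidence intervals. Cost: one model term and one imprecise table. No change to the sample size is needed.
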